## Abstract

**Background:**

The global rise in diabetes, particularly in India, poses a significant public health challenge, with factors such as limited awareness, financial strain, and cultural considerations hindering its effective management. Although lifestyle changes have shown promising results, their consistent implementation and maintenance continue to pose challenges. Most studies have focused primarily on dietary modifications, overlooking other essential aspects of lifestyle intervention. The DiRemI study aims to address these gaps by evaluating the efficacy of a comprehensive one-year program that combines diet, exercise, psychological support, and medical management to achieve weight loss, diabetes remission, and improved glycemic control among patients with type 2 diabetes (T2D) in India, while also considering the unique needs of the Indian population.

**Methods:**

The DiRemI study is a prospective, open-label, matched-group trial aimed at assessing the impact of a one-year online integrated intensive lifestyle intervention (ILI) comprising dietary modifications, physical activity, psychological support, and medical management on weight loss and remission in adult T2D patients (aged 30–70 years), with a body mass index (BMI) between 25 and 35 kg/m^2^, and disease duration of <15 years. ILI will be compared with routine medical care (RMC). Participants will be recruited from three clinics: one providing ILI and two others providing RMC. The co-primary outcome will be weight loss and remission at 12 months, with a follow-up at 18 months. The proposed sample size is 360 participants (180 each in intervention and control group).

**Discussion:**

The DiRemI study represents the first large-scale remission study in India to show the effectiveness of an integrated approach in the remission and management of T2D and its complications. The findings of this study hold the potential to report evidence-based strategies for managing T2D both in India and globally, thus alleviating the substantial burden of diabetes on public health systems.

**Trial registration:**

Clinical Trials Registry, India (Registered Number: CTRI/2023/06/053885).

## Introduction

The worldwide prevalence of diabetes mellitus is increasing, posing a significant threat to public health. In 2021, the estimated global incidence of diabetes in adults was 537 million, with 90% of cases of type 2 diabetes (T2D) [1, 2]. According to the International Diabetes Federation (IDF) (2019), globally, India has the second-highest number of individuals with diabetes at 77 million and the number is projected to increase to nearly 134 million by 2045 [3]. It further estimates that India contributed the highest to diabetes-associated complication deaths in South Asia in 2019 [3]. Therefore, the overbearing public health burden of T2D in the region necessitates effective management and intervention strategies.

Efficient management of diabetes and its associated complications in India is hindered by several factors, including limited awareness of diabetes, its risk factors, prevention methods, insufficient healthcare infrastructure, economic challenges, and non-adherence to medication. [4]. Patients in India face significant financial strain due to out-of-pocket expenses, particularly in the absence of adequate insurance schemes and policies [5, 6]. In addition, social stigma adds to the mental stress they experience [4]. All of these factors can lead to underdiagnosis and poor treatment-seeking behaviour, leading to an increased risk of complications and comorbidities [7]. India is a country with diverse culture and food habits with studies indicating that this population is unique in dealing with emotional distress, perceived stress, and other psychological conditions related to T2D [8, 9]. Further, the South Asian phenotype and genotype are distinct, as evidenced by central obesity, even at normal BMI, which makes them more prone to diabetes and its complications at relatively low BMIs in both native and immigrant populations [8]. Therefore, there is an urgent need to address the public health concerns surrounding T2D in India.

Pharmacological management can delay, but not entirely prevent, the development of diabetes-related complications. Achieving T2D remission, which is defined as maintaining HbA1C levels below 6.5% for at least three months without the use of glucose-lowering medications, may be the most effective way to reduce the morbidity and mortality associated with the disease [10, 11]. T2D remission has been reported in patients treated with metabolic surgery, intensive pharmacotherapy, and significant lifestyle modifications [12], each with its own merits and limitations. Among them, lifestyle interventions may be the most economical.

Previous studies using intensive lifestyle interventions (ILI) have reported successful T2D remission. However, despite considerable evidence of remission, lifestyle management is not considered the standard first-line of care because of the challenge of making patients adopt and adhere to the lifestyle changes, which includes complete dietary modification, behavioural changes, a specific exercise regime, regular monitoring of blood sugar levels, and staying optimistic and motivated for a longer duration [13–15].

A systematic review by Karera et al. (2023) [16] indicated that most studies employing ILI concentrated on dietary modifications through total diet replacement and medication cessation in individuals with higher body mass indices (>27 kg/m^2^) and shorter disease durations. Notably, none of these studies considered the mental health and existing dietary patterns of the study participants, while only one study by Taheri et al. (2018) [17] included exercise as a part of ILI. This highlights the lack of studies using a comprehensive approach incorporating diet, exercise, and psychological support, along with medical management for patients with a longer duration of T2D.

The Diabetes Remission in India (DiRemI) study aims to evaluate the efficacy of the one-year Freedom from Diabetes protocol, which integrates diet, physical activity, psychological support, and medical management, compared to standard medical care to achieve weight loss, diabetes remission, and improved glycemic control in patients with T2D in the Indian population. The program is individualized & designed considering the cultural barriers, food choices, physical activity challenges, and psychological aspects of individuals with T2D in India.

### Specific objectives (as specified during ethics submission)

The primary objective of the intervention is to achieve a weight reduction of ≥ 10% and an HbA1c level of <6.5% without pharmacotherapy, with the ultimate goal of achieving diabetes remission. The secondary objective of the intervention is to evaluate its effect on other aspects of diabetes outcomes, including mental health (anxiety and depression), comorbidities (hypertension and dyslipidaemia), diabetes-related complications (nephropathy), and biochemical parameters (serum lipids, liver function tests, and kidney function tests).

## Methods

### Design

The present study is a prospective, open-label, matched control trial. Ethical approval for the study was granted by the Institutional Ethics Committee (IEC) (Ref. no. FFDRF/IEC/2023/3). The trial is prospectively registered with the Clinical Trials Registry-India (CTRI) (Ref. No. CTRI/2023/06/053885) (S1 File). This study will adhere to the standards for clinical research outlined in the Declaration of Helsinki. The protocol is designed according to the SPIRIT guidelines (S1 Checklist).

### Setting and eligibility criteria

The proposed study will be conducted at the Freedom from Diabetes Clinic, which operates on an online subscription-based model of 1-year duration for the management of diabetes (intervention group). Additionally, the study will include participants from two private clinics in Pune and Ahmedabad (India) (Control Group), which provide standard medical care based on established guidelines for individuals with diabetes. All individuals with T2D who enrol in these centres between March and August 2024 and meet the eligibility criteria will be recruited for this study Table 1.

**Table 1 pone.0306394.t001:** Eligibility criteria for the DiRemI study.

Inclusion Criteria	Exclusion Criteria
Age between 30 and 70 years	Pancreatitis or drug-induced diabetes (Steroids)
Confirmed diagnosis of type 2 diabetes, which may be managed with oral hypoglycemic agents, insulin, Ayurvedic antidiabetic medications, or have an HbA1c level of ≥ 48 mmol/mol (6.5%) with or without medication	Other types of diabetes (type 1 diabetes mellitus, diabetes insipidus, maturity-onset diabetes of the young, latent autoimmune diabetes in adults, or Gestational Diabetes)
Body mass index (BMI) between 25 kg/m^2^ and 35 kg/m^2^	Advanced complications related to nephropathy (eGFR<30 mL/min/1.73 m^2^, urine microalbumin >1000 mg), retinopathy (severe non-proliferative diabetic retinopathy and proliferative diabetic retinopathy), neuropathy (peripheral artery disease or diabetic neuropathy resulting in complete numbness and loss of sensation, amputations, ulcers, foot deformities, Charcot’s foot)
Duration of type 2 diabetes less than 15 years	History of heart attack, cardiac arrhythmia, bypass or stent placement surgery, ischemic heart disease, angina (class II or III), myocardial infarction within the previous 6 months, reported ejection fraction <40%, abnormal ECG, and positive stress test results (moderate or severe)
Ready to provide written informed consent	Known history of cancer
Agree to undergo the examination, lifestyle intervention program, and post-program evaluation	Pregnant and lactating women
Well-oriented in time, space, and as a person	Patients who have required hospitalization for any diabetes-related complications in the last 6 months or for depression or are on antipsychotic drugs

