### Control group (Routine medical care)

The control group will receive routine medical care along with education for management of T2D and its associated comorbidities based on current clinical guidelines.

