### Outcome measures

The primary outcome measures are a) Weight loss of more than or equal to 10% and b) Remission of T2D (HbA1c less than 6.5% for at least 3 months without medication). Secondary outcomes include a) reduction in dosage and/ or frequency/ class of drug or complete stoppage of diabetes medication, b) improved glycemic control (HbA1c less than 7% with or without medication), c) reduction in fasting glucose levels (below 126 mg/dl) and PP blood glucose levels (below 200 mg/dl) with or without glucose-lowering medications), d) improvement in diabetes-related complications (nephropathy- improvement in terms of eGFR>90 mL/min/1.73m^2^), e) improvement in comorbidities (hypertension- blood pressure ≤140/90 and dyslipidaemia- Total cholesterol <200 mg/dl, triglycerides <150 mg/dl, and HDL >40 mg/dl for males and >50 mg/dl for females), and f) improvement in mental health outcomes (anxiety and depression- Reduction in the score—below 10).

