### Statistical analyses

Primary outcome measures will be analysed using two-sided statistical tests with a type I error rate of α = 0.05. Primary analysis will be performed using the intention-to-treat method. Categorical data will be compared between the two groups using chi-square or Fisher’s exact tests. Continuous data will be evaluated using parametric or non-parametric tests based on data distribution.

For outliers (± 3 standard deviation), efforts will be made to cross-check and obtain the correct values. Failing this, the case will be considered as missing data. In the case of random missing values, two separate analyses will be performed: one including the cases with missing data by choosing pairwise deletion and the other excluding it using listwise or case-wise deletion. A complete case analysis will be considered if differences are observed between the two analyses. In the case of non-random missing values, the imputation method may be used by replacing the missing value with the mean for that variable.

Potential adjustments for baseline values, age, gender, and disease duration may be considered. Multivariable linear and logistic regression analyses will be used to determine predictors of remission. Finally, subgroup analyses may be performed based on factors such as gender, age, comorbidity, diagnosis length, and severity to investigate potential variations in treatment responses.

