The importance of mental health is unparalleled and closely connected to effective T2D management. In addition to dietary and exercise adjustments, this trial encompasses a multifaceted approach to both physical and mental well-being, which has not been extensively addressed in previous studies. Research has demonstrated that participants with T2D who experience depression are twice as likely to exhibit non-adherence to medications for diabetes, blood pressure, and cholesterol when compared to non-depressed participants [37]. Moreover, individuals with poorer diabetes self-care tendencies generally exhibit heightened levels of psychological distress, diminished social support, and decreased self-efficacy [38]. In the proposed trial, T2D participants will receive psychological support from trained psychologists to help address and cope with life stressors and achieve optimal disease management.

Another unique feature of our study is the focus on medical management. Unlike previous studies on ILI [17, 39] that completely withdrew all diabetes medicines before the commencement of the trials, in our study, the physician will ensure systematic tapering of medications based on daily reported blood sugar levels. This approach will ensure appropriate medical management of participants with a longer duration of diabetes and, hence, more complications. Furthermore, medical management will address and correct nutritional deficiencies through supplementation.

Our study differs from many other studies on ILI, which have generally focused on specific population demographics (e.g. younger age and newly diagnosed T2D) [35, 39, 40] and limited interventions targeting specific features, such as low/very low-calorie diets, diet replacement, and weight loss, with less emphasis on physical activity and intensive exercise training [36, 41]. Our study represents a unique approach that incorporates a comprehensive, personalised methodology specifically designed to accommodate the distinct features of each participant, with a particular focus on a demographically varied group of individuals aged between 30 and 70 years, who have been living with diabetes for up to 15 years.

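### Table 1 sets no clear minimum HbA1c for drug-treated participants, so a clinic difference in the share entering below 6.5% can pass into the non-randomised remission comparison

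*Protocol article*

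**What the plan says.** **Entry.** The diagnosis row of Table 1 (Setting and eligibility criteria) has two parts. The first is "Confirmed diagnosis of type 2 diabetes, which may be managed with oral hypoglycemic agents, insulin, Ayurvedic antidiabetic medications". The second follows directly: "or have an HbA1c level of ≥ 48 mmol/mol (6.5%) with or without medication". Where the two parts meet, the row runs "may be managed with oral hypoglycemic agents, insulin, Ayurvedic antidiabetic medications, or have an HbA1c level of ≥ 48 mmol/mol (6.5"%). No other inclusion or exclusion row mentions HbA1c.

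**Outcome.** Under Outcome measures, the second primary outcome is "Remission of T2D (HbA1c less than 6.5% for at least 3 months without medication"). The Specific objectives put it the same way: "an HbA1c level of <6.5% without pharmacotherapy". Neither refers to HbA1c or treatment at entry.

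**Care in the two groups.** In the programme, according to the Discussion, "the physician will ensure systematic tapering of medications based on daily reported blood sugar levels". For the comparison clinics, the section on the control group says "The control group will receive routine medical care along with education for management of T2D"; no tapering is described there.

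**Comparison.** The groups come from different clinics. The random numbers under Sampling and recruitment process pick people from each clinic's list of eligible patients and do not allocate treatment. The design is called matched, but HbA1c is not named as a matching variable. Under Statistical analyses, "Potential adjustments for baseline values, age, gender, and disease duration may be considered".

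**The concern.** The entry rule and the primary outcome use the same 6.5% figure but do not fit together. Someone who enters at 6.2% on a drug, stops it and stays at 6.4% is a remission success, although measured HbA1c has risen slightly. Someone who enters well above 6.5% has to lower HbA1c and also come off drugs. The remission proportion pools these two kinds of success.

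In a randomised trial the mix would be balanced on average. Here it depends on who subscribes to an online programme and who attends two private clinics. If one source has more people already at the HbA1c target, its remission rate can be higher for that reason alone, and the plan commits to nothing that would remove the difference.

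**Working it through.** **1. Reading the row.** *Or* makes HbA1c of at least 6.5% an alternative to drug treatment, not an added condition. The closing words about medication let treated people qualify by the HbA1c route, but do not close the treatment route to those below 6.5%. Each case against the remission definition:

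| At entry | Eligible? | HbA1c half met at entry? | Medication-free half met at entry? |
|---|---|---|---|
| On drugs, HbA1c ≥6.5% | Yes | No | No |
| On drugs, HbA1c <6.5% | Yes, read literally | Yes | No |
| No drugs, HbA1c ≥6.5% | Yes | No | Yes |
| No drugs, HbA1c <6.5% | Not on the natural reading; not clearly excluded, because of *may* | Yes | Yes |

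The second line carries the concern. The fourth is a drafting gap.

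**2. How the mix enters the comparison.** Let q be the share of a group entering below 6.5%, a the remission rate among those entering at 6.5% or above, and b the rate among those entering below it. The group's remission rate is

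R = (1 − q)·a + q·b.

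If the programme had no effect, a and b would be the same in both groups, and

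R(programme) − R(control) = [q(programme) − q(control)] × (b − a).

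This is zero when the shares are equal and has the sign of the difference in shares when b exceeds a.

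**3. Illustration.** The article gives none of q, a or b, so there is no plan figure to reproduce and every rate here is an assumption. Take a = 5% and b = 50% to 80%.

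- Shares 20% and 10%: 0.10 × 0.45 = 4.5 points; 0.10 × 0.75 = 7.5 points.
- Shares 30% and 10%: 0.20 × 0.45 = 9 points; 0.20 × 0.75 = 15 points.
- Shares reversed: the same sizes, against the programme.

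**4. Equal shares, tapering in one group only.** Keep a = 5% in both groups, but let b be 50% in the programme and 5% in control, or 80% and 10%. The difference is q × [b(programme) − b(control)].

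- q = 10%: 0.10 × 0.45 = 4.5 points; 0.10 × 0.70 = 7 points.
- q = 20%: 9 to 14 points.
- q = 30%: 13.5 to 21 points.

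This is not case-mix bias, since drug withdrawal is part of the programme. It shows how far a remission difference could arise from withdrawal among people already at target, and so why results by entry HbA1c are needed to interpret it.

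**5. Size of the restricted set.** The plan has 180 per group and allows for 30% loss: 180 × 0.70 = 126 completers. If 20% enter below 6.5% (assumed), 126 × 0.80 ≈ 101 remain. Counting everyone enrolled, as under intention to treat, 180 × 0.80 = 144 per group.

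**The case against.** The strongest reply is that the outcome is sound as it stands. The Introduction defines remission as an off-drug state, with no reference to where the person started. Holding 6.2% on drugs and holding it off drugs are different states, and reaching the second is a real change that the programme sets out to produce. That stands. The concern is not that the definition is wrong, nor that a fall in HbA1c must be required.

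Three stronger readings are tempting, and the article does not support them.

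- *Treated people below 6.5% are automatic successes with no improvement.* They are not. They must stop all glucose-lowering drugs and stay below 6.5% for three months. Only the absence of a fall in measured HbA1c can be claimed.
- *The trial admits people already in remission.* That needs a loose reading of *may*. The natural reading is treated, or at 6.5% or above, which leaves out an untreated person below 6.5%. The wording merely fails to exclude that person clearly.
- *The remission effect is inflated by 5 to 24 points.* Assumed shares of 10% to 30% and off-drug success of 50% to 80% give 0.10 × 0.5 = 5 and 0.30 × 0.8 = 24 points. This is a contribution to one group's rate from unanchored inputs, not a between-group bias.

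It can also be said that the article admits the lack of randomisation, calls the groups matched, and may leave sensitivity analyses and matching variables to documents not shown. If HbA1c is matched, the case-mix part shrinks. But the article itself fixes both the entry row and the outcome, and it makes baseline adjustment optional. The interaction of the three is there on the page.

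**Conclusion.** The point holds in limited form. Read literally, Table 1 lets in treated people below 6.5%, and remission takes no account of entry HbA1c. With non-randomised groups, HbA1c not named for matching and adjustment only optional, a clinic difference in the share entering below 6.5% can appear as a remission effect.

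The size cannot be stated from the article. It is zero if the shares are equal and, on the assumptions above, 4.5 to 15 points for a difference in shares of 10 to 20 points, in either direction. Those figures also assume that b is the same in both groups. With no tapering described in control, b may be much lower there, and the result then depends mainly on the programme's own share. This should be corrected, but it does not invalidate the remission outcome.

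**What to change.** 1. **Entry row.** Reword the row so that it says unambiguously whether the 6.5% limit applies to people on drugs. State that people below 6.5% on no glucose-lowering drug are not eligible. Recruitment was due to run from 1 March to 31 August 2024, so some may already be enrolled. Those should not be counted as remission successes in either group, because they met the HbA1c and no-medication terms at entry.

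2. **Analysis.** Keep the full-population remission analysis. Replace the optional wording with a definite adjustment for baseline HbA1c and baseline medication. Report remission by group separately for entry HbA1c below 6.5% and at or above it. Pre-specify the subset at 6.5% or above as the key sensitivity analysis. Moving the whole remission claim to that subset is not needed: it would change the target population and drop well-controlled treated people for whom coming off drugs is a substantial change.

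**Cost.** A change to one table row, which during recruitment is an eligibility amendment, and a few added analyses. No new data are needed: HbA1c is collected at the start, and the secondary outcome on reducing diabetes medication already requires drug use at entry. The restricted analysis is less precise, with about 101 of 126 completers per group under the 20% assumption. If control remissions are few, the adjusted model may need a method suited to sparse events.

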### Sample size determination

We calculated the sample size for our study using Bonferroni correction to adjust for two primary outcome measures: weight and HbA1c. With an overall alpha level of 0.05, the adjusted significance level for each outcome was set to 0.025. Assuming a power of 95%, the required sample sizes were determined based on Cohen’s d effect sizes of 0.445 for weight and 0.635 for HbA1c, based on a previous study by Lean et al. (2018) [18]. The calculations indicated a sample size of 132 participants per group for weight and 65 participants per group for HbA1c level. To ensure adequate power for both outcomes, we selected the larger sample size requirement, resulting in a total sample size of 132 participants per group. To account for the potential dropout and loss to follow-up of 30%, the final sample size was estimated at 360 (180 in each group).

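### The stated sizes of 132 and 65 per group do not contain the Bonferroni correction at two-sided 0.025, and 180 per group does not cover 30% loss, so power for weight is about 90%, not 95%

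*Protocol article*

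**What the plan says.** All the figures are in the protocol article, Methods, Sample size determination, except the sidedness of the tests.

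- Multiplicity: "We calculated the sample size for our study using Bonferroni correction to adjust for two primary outcome measures: weight and HbA1c".
- Level per outcome: "With an overall alpha level of 0.05, the adjusted significance level for each outcome was set to 0.025".
- Power: "Assuming a power of 95%, the required sample sizes were determined".
- Effect sizes: "Cohen’s d effect sizes of 0.445 for weight and 0.635 for HbA1c".
- Result: "The calculations indicated a sample size of 132 participants per group for weight and 65 participants per group for HbA1c level". The larger figure, 132, is carried forward.
- Loss: "To account for the potential dropout and loss to follow-up of 30%, the final sample size was estimated at 360 (180 in each group").

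The sample size section does not say whether its calculation is one- or two-sided. The Statistical analyses section does so for the tests: "Primary outcome measures will be analysed using two-sided statistical tests with a type I error rate of α = 0.05". It does not repeat the split to 0.025.

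**The concern.** The paragraph gives every input and every result, so it can be checked, and two of its steps do not follow. The sizes should reflect the level of 0.025 that the text says was used, and they do not. The enrolment figure should leave 132 per group after 30% loss, and it does not.

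Both errors push the size down. This paragraph is the only justification for 360 participants, and weight is the outcome that sets the number. If the text is taken at its word, a reader believes the trial has a 5% risk of missing the assumed weight effect at a multiplicity-adjusted level. The design does not provide that.

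**Working it through.** **Inputs.** d = 0.445 (weight) and 0.635 (HbA1c); power 95%; level 0.025 per outcome; 30% loss; 180 per group with equal allocation (all from Sample size determination). Two-sided tests (from Statistical analyses).

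**Formula.** For two equal groups and a standardised difference d, the normal approximation is n per group = 2(z₁₋α/₂ + z₀.₉₅)²/d². Results are cross-checked with the noncentral t distribution.

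**Step 1: reproduce the printed figures.** At two-sided 0.05, z = 1.960 and 1.645, so (3.605)² = 12.995.

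- Weight: 2 × 12.995/0.445² = 131.2, rounded up to **132**
- HbA1c: 2 × 12.995/0.635² = 64.5, rounded up to **65**

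Both printed figures appear. The t-based solutions are 132.2 and 65.4, which round up to 133 and 66. One-sided 0.025 uses the same critical value and gives the same sizes.

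**Step 2: use the level the text claims.** At two-sided 0.025, z = 2.241 and 1.645, so (3.886)² = 15.103.

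- Weight: 2 × 15.103/0.445² = 152.5, rounded up to **153** (t: 154)
- HbA1c: 2 × 15.103/0.635² = 74.9, rounded up to **75** (t: 77)

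The shortfall is 21 per group for weight and 10 for HbA1c. The choice between normal and t moves the sizes by only 1 or 2, so it does not explain the gap.

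**Step 3: loss to follow-up.**

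- Needed to retain 132: 132/0.70 = 188.6, so 189 per group (378 in total)
- Retained from 180: 180 × 0.70 = 126, which is 6 short of 132
- Loss that 180 can absorb while keeping 132: 1 − 132/180 = 26.7%
- The incorrect but common inflation, 132 × 1.30 = 171.6, rounds up to 172 and does not give 180 either
- Needed for the corrected weight requirement: 153/0.70 = 218.6 or 154/0.70 = 220, so 219 to 220 per group (438 to 440 in total)

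**Step 4: power delivered.**

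| Outcome (d) | Evaluable per group | Two-sided level | Power, normal | Power, t |
|---|---|---|---|---|
| Weight (0.445) | 132 | 0.05 | 95.1% | 95.0% |
| Weight (0.445) | 126 | 0.05 | 94.2% | 94.0% |
| Weight (0.445) | 132 | 0.025 | 91.5% | 91.3% |
| Weight (0.445) | 126 | 0.025 | 90.2% | 89.9% |
| HbA1c (0.635) | 126 | 0.025 | 99.7% | 99.7% |

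Most of the drop for weight comes from the level (about 95% to about 91.5%). The loss shortfall takes a further 1.4 points or so.

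**The case against.** The arithmetic is not in dispute. The case against rests on what may be concluded from it.

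- **The cause is not proven.** One-sided 0.025 gives the same 132 and 65, and could be a Bonferroni split of a one-sided 0.05. This stands as far as it goes: the article cannot show which calculation was run. It does not rescue the paragraph, because the primary tests are declared two-sided, and at two-sided 0.025 the sizes are 153 and 75.
- **The 90% is conditional.** It applies if each outcome is tested at 0.025 and the full 30% is lost. The Statistical analyses section can be read as testing each outcome at 0.05, which gives about 94% with 126 per group. This is correct, but 94% is still below 95%, and on that reading the Bonferroni control claimed in the sample size section is gone. No reading gives 95% power after 30% loss from 180.
- **The loss error is small.** It costs about 1.4 points of power and 9 participants per group (189 − 180). That is fair. The level is the larger of the two errors.
- **The practical effect is modest.** Power near 90% for weight and above 99% for HbA1c is respectable. That bears on how much the error matters, not on whether the text is right.
- **The power figure is not for the declared outcomes.** Outcome measures defines the primary outcomes as binary (weight loss of at least 10%, and remission), while the d values describe mean differences. This is a fair limit on any figure quoted here: about 90% is the power for d = 0.445 on the plan's own terms, not for the binary comparison.

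**Conclusion.** The point holds. The printed sizes match an uncorrected two-sided 0.05 and not the two-sided 0.025 that the two sections together imply. Enrolling 180 per group does not leave 132 after 30% loss.

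On the plan's own assumptions (d = 0.445, two-sided 0.025, 30% loss, equal groups), power for weight is about 90%. The false-negative risk is therefore about 10%, twice the stated 5%. Delivering the stated 95% would take 219 to 220 per group instead of 180. HbA1c is not affected in practice under its assumed d.

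The consequence is moderate, since the trial remains reasonably powered for the assumed effects. The stated justification for its size is nevertheless incorrect and should not stand.

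**What to change.** Keep 360 participants and rewrite the Sample size determination paragraph so that its figures agree. Suggested wording:

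> With a two-sided level of 0.025 for each of the two outcomes (Bonferroni, overall 0.05), 95% power would require 153 evaluable participants per group for weight (d = 0.445) and 75 for HbA1c (d = 0.635). We will enrol 180 per group. If 30% are lost, 126 per group remain, which gives about 90% power for weight and over 99% for HbA1c at these effect sizes.

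Remove the claim of 95% power at the adjusted level and the claim that 180 per group allows for 30% loss from 132.

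The cost is the wording of one paragraph and a slightly less favourable stated power for weight. No participants are added and no procedure changes.
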